**Discussion:**

Results of this pilot trial will help determine whether or not to proceed with a full trial after the pilot trial, and if so, whether revisions should be made to the study protocol and procedures before conducting a full randomized controlled trial. Additionally, they are expected to provide insights into whether changes in psychological, behavioral and biological parameters can be attributed to the probiotic intervention.

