Maternal lifestyle	Smoking (yes/no)	Baseline value	Proportion of participants smoking
	Alcohol (yes/no)	Baseline value	Proportion of participants drinking alcohol
Pregnancy characteristics	Occurrence of infections during pregnancy	Final value	Proportion of participants reporting infections (i.e. influenza, fever, diarrhea) throughout the study
Delivery characteristics	Gestational age	Final value	Gestational age at delivery
Pregnancy and delivery complications	Number of pregnancy and delivery complications (i.e. hypertensive disorders of pregnancy (pregnancy induced hypertension, preeclampsia, eclampsia, hemolysis - elevated liver enzymes - low platelet count (HELLP) syndrome), gestational diabetes mellitus, preterm birth, cesarean section, retention placentae, hemorrhage postpartum, small or large for gestational age (birth weight < p10 or > p90), puerperal fever, prolonged labor, premature rupture of membranes)	Final value	Proportion of participants diagnosed with pregnancy or delivery complications at delivery
Infant antibiotic use	Number of antibiotics used	Final value	Proportion of infants receiving antibiotics during first month of life
Depression	Edinburgh Postnatal Depression Scale (EPDS) score	Change from baseline to t1 and t4	Mean (SD)/median (IQR)
Depression/cognitive reactivity	Leiden Index of Depression Sensitivity-Revised (LEIDS-R) score	Change from baseline to t1 and t4	Mean (SD)/median (IQR)
Pregnancy related anxiety	Pregnancy Related Anxiety Questionnaire-Revised (PRAQ-R) score	Change from baseline to t1	Mean (SD)/median (IQR)
General anxiety	State-trait Anxiety Inventory (STAI-S) score	Change from baseline to t1 and t4	Mean (SD)/median (IQR)
Pregnancy-related daily hassles	Pregnancy-related daily hassles (PES) score	Change from baseline to t1 and t4	Mean (SD)/median (IQR)
General daily hassles/stress	Daily Hassles List (APL) score	Change from baseline to t1 and t4	Mean (SD)/median (IQR)
Mother to infant bonding	Maternal Antenatal Attachment Scale (MAAS) score	Change from baseline to t1	Mean (SD)/median (IQR)
	Maternal Postnatal Attachment Scale (MPAS)	Change from t3 to t4	Mean (SD)/median (IQR)
Biological samples	Maternal fecal samples (microbiota)	Change from baseline to t1	Relative abundance and diversity of bacteria at phylum up to genus level
	Maternal vaginal samples (microbiota)	Change from baseline to t1	Relative abundance and diversity of bacteria at phylum up to genus level

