	Maternal hair (cortisol)	Change from baseline to t1	Mean (SD)/median (IQR)
	Fecal sample infant (microbiota)	Change from t3 to t4	Relative abundance of bacteria at phylum up to genus level
Cry diary	Duration (hours/minutes) of crying during 3 days	Final value	Mean (SD)/median (IQR)

^a^Baseline: t0; time point 1: t1, time point 3: t3, time point 4: t4

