#### Secondary outcomes

Although the aim of this pilot trial is to assess the feasibility and acceptability of running a definitive trial, the secondary psychological, behavioral and biological outcomes will be analyzed to mimic the definitive trial. All analyses of the secondary outcomes will hence be viewed as preliminary and thus interpreted with caution.

Outcomes will be analyzed per-protocol and by intention to treat (ITT). For the per-protocol analysis, participants who are found ineligible after randomization or deviated from the probiotics/placebo product intake (i.e. less than 80% intake) will be excluded from the main analysis. For the ITT analysis, all randomized participants, regardless of protocol adherence or dropouts (i.e. participants who withdraw consent for continued follow up), will be included in the main analysis. Participants will be analyzed according to the group to which they were originally allocated. In case of missing data, missing values will be imputed. Student’s *t* test will be used to analyze normally distributed data and the nonparametric Mann–Whitney U test will be used to analyze non-normally distributed data. For comparisons of more than two groups (e.g. differences in the relative abundance of bacteria at the level of phylum up to the level of order in microbial samples), analysis of variance with Tukey’s post-hoc test of the intervention and placebo group at the primary endpoint will be compared using a one-way analysis of covariance (ANCOVA) model, where the covariate will be the baseline score. In addition, the effect size will be computed to estimate the required sample size for the future large-scale trial. The significance level for statistical analysis is set at *p* < 0.05.

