### Maternal vaginal and gut microbiota

Previous studies suggest that maternal stress during pregnancy is associated with vaginal [89] and intestinal dysbiosis [87]. The collection of maternal vaginal and gut microbiota samples will help determine whether mothers receiving a probiotic have vaginal and microbial compositions characterized by more beneficial bacteria, compared to mothers in the placebo group.

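### Bacterial taxa are compared at a flat p < 0.05 with a Tukey test that does not control error across taxa, over a taxonomic range that Table 2 contradicts (minor)

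*Protocol article*

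**What the plan says.** Three places in the Protocol article bear on this.

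- **Statistical analysis, Secondary outcomes.** Two-group comparisons use Student's t test or the Mann-Whitney test. A separate rule begins "For comparisons of more than two groups" and gives as its example "differences in the relative abundance of bacteria at the level of phylum up to the level of order in microbial samples". The method is analysis of variance with "Tukey’s post-hoc test of the intervention and placebo group at the primary endpoint", and the same sentence runs on into an ANCOVA with the baseline score as covariate. The section ends with "The significance level for statistical analysis is set at" p < 0.05. Outcomes are analysed both per protocol and by intention to treat. No adjustment across taxa or sample types is given.
- **Table 2, Biological samples.** Maternal stool and maternal vaginal samples: "Relative abundance and diversity of bacteria at phylum up to genus level", as change from baseline to t1. Infant stool: "Relative abundance of bacteria at phylum up to genus level", as change from t3 to t4.
- **Stated use.** The Discussion section on maternal microbiota says the samples "will help determine whether mothers receiving a probiotic have vaginal and microbial compositions characterized by more beneficial bacteria". The abstract expects insight into "whether changes in psychological, behavioral and biological parameters can be attributed to the probiotic intervention". Against this, the analysis section calls all secondary analyses preliminary, and the section on secondary outcomes sets no criteria for treatment success on any of them.

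**The concern.** A separate test on each taxon makes a large family of tests, and a fixed 5% level per test leaves the error over that family uncontrolled. Tukey's test looks like a safeguard but works in a different direction: it adjusts for comparing several groups on one outcome. With two arms there is one pairwise comparison per taxon and nothing for it to adjust.

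The two taxonomic ranges also leave the family open. Stopping at order or going on to genus can change the number of tests a great deal, and the choice could be made after the data are seen.

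At stake is how the mechanistic results are read. A taxon that crosses 0.05 by chance could be reported as a sign that the product shifts the microbiota, and could shape the hypotheses of the full trial.

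**Working it through.** **Inputs from the article:** level 0.05 per test; two arms; three sample types (maternal stool, maternal vaginal, infant stool); no adjustment across taxa. The level is a chosen value, so there is no derived figure to reproduce.

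**Inputs not in the article, assumed:** 5 to 50 taxa per sample type, so 3 × 5 = 15 to 3 × 50 = 150 tests; correlation between test statistics from 0 to 0.7. Each taxon is counted once, although two analysis sets are planned.

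**Step 1, what Tukey adjusts.** With k groups there are k(k − 1)/2 pairwise comparisons per outcome. For k = 2 this is 1, so the per-taxon level stays at 0.05. If the groups were instead meant to be bacterial groups, Tukey would compare taxa with one another, which is not the treatment question.

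**Step 2, independent tests.** Under no effect, P(at least one) = 1 − 0.95^m, and the expected number of false positives is 0.05 × m.

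- m = 15: 1 − 0.95^15 = 53.7%; expected 0.75
- m = 60: 1 − 0.95^60 = 95.4%; expected 3
- m = 150: 1 − 0.95^150 = 99.95%; expected 7.5

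**Step 3, dependent tests.** Nested ranks and relative abundances are not independent. Simulating two-sided normal test statistics with one common correlation (20,000 draws) gives this chance of at least one false positive:

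| Tests | corr. 0.3 | corr. 0.5 | corr. 0.7 |
|---|---|---|---|
| 15 | 46% | 36% | 25% |
| 60 | 85% | 66% | 43% |
| 150 | 98% | 85% | 56% |

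Dependence lowers this chance but leaves the expected number of false positives unchanged. Every cell is at least five times the nominal 5%.

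**Step 4, the range.** The analysis section's example stops at order; Table 2 goes to genus for all three sample types. The product's strains, listed under Probiotic/placebo formulations, belong to three genera (Bifidobacterium, Lactobacillus, Lactococcus), so the analysis section's example never reaches the rank at which the product is described.

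**Step 5, the covariate.** Maternal samples have a baseline at t0. Infant samples are taken at t3 and t4, both after birth, so no pre-intervention value exists and the baseline ANCOVA cannot be applied to them.

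**Step 6, the alternative.** Benjamini-Hochberg control at 5%, simulated with no effect and independent tests (10,000 draws), gives at least one flagged taxon in 4.9% to 5.2% of runs for 45 to 150 taxa. Applied separately in three independent sample types, the overall chance is 1 − 0.95^3 = 14.3%.

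A short named list also needs care if left unadjusted. Two genera in three sample types plus diversity in the two maternal types make 8 tests, 1 − 0.95^8 = 33.7%. The three product genera in three sample types make 9 tests, 1 − 0.95^9 = 37.0%; at 0.05/9 = 0.0056 each, this falls to 4.9%.

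**The case against.** The strongest reply is that nothing depends on these tests. The comparisons are described as exploratory and preliminary, and no success criteria are set. The progression criteria in Table 1 use microbiota only as a sample-collection rate. This stands, and it is why the point is minor.

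A second reply is that a condensed article may leave a false-discovery method to a full protocol or analysis plan. That would answer a complaint about silence. Here the article does name a level, a post-hoc test and their use on taxa, and that combination does not do the job.

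A third is that Table 2's range sits in a column on aggregation, so the family of tests may be the smaller one ending at order. That is possible. It shows that the range needs to be stated once, and even 15 independent tests exceed 50%.

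A reader might also infer more than the article supports:

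- **That false positives are close to certain.** This needs roughly 60 or more nearly independent tests. The number of taxa is not given, and correlation pulls the figure down substantially.
- **That no contrast is named.** Intervention versus placebo is named. The fault is the confused sentence around it.
- **That lactobacilli and bifidobacteria carry the hypothesis.** They appear in the Discussion as background on infants of stressed mothers. The maternal aim names no genus, and the product contains a third.

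**Conclusion.** The point holds as a minor one. The stated method does not control error across taxa, is written for a number of groups the trial does not have, and covers a range that conflicts with Table 2. At least one chance finding is more likely than not over much of the assumed range, though not all of it: with only 15 tests and correlation of 0.3 or more, the chance falls below one half. These figures rest on assumed taxa counts and a single common correlation; what does not depend on them is that the error across taxa is uncontrolled. The likely harm is over-reading of mechanistic results, not a wrong decision about the full trial.

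**What to change.** In the Secondary outcomes part of the Statistical analysis section:

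1. Replace the sentence on more than two groups with a two-arm comparison for each taxon, baseline-adjusted for the maternal samples. Describe the infant samples separately, since they have no pre-intervention value.
2. State one taxonomic range and make Table 2 agree with it.
3. Drop Tukey and apply Benjamini-Hochberg control across taxa within each sample type, with the false-discovery level stated in advance.
4. If the sponsor wishes to give some taxa priority as beneficial, for example the product genera, name them before the data are seen. Report these, and diversity, as estimates with confidence intervals or with adjustment.
5. Bring the wording of the abstract and of the Discussion on maternal microbiota into line with the preliminary label.

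The cost is a few sentences and a standard step in the analysis code, with no new samples or measurements. The drawback is that fewer taxa will be flagged, and with 20 women per arm some real shifts may go unflagged.

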### Data monitoring and auditing

The Sponsor will appoint a monitor independent of the investigators, who will visit the trial site before initiation of the study and once during the recruitment of participants. The monitor will check on adherence to the study protocol, reporting of adverse events (AEs) and CRFs, verification of the completeness of the trial master file and the quality and completeness of the data, and will examine source documents and determine whether the data reported in the Microsoft Excel spreadsheet charts are accurate. Given the expected relatively short duration of the pilot study and that this trial was categorized as minimal-risk research by the Medical Ethics Committee (METC), no official data monitoring committee will be installed to periodically review the accumulating data or to determine whether the pilot should be modified or discontinued.

### Potential harms

We consider this study to pose negligible risk to participants. Participants in the probiotic arm may experience incidental sensations of bloating and change in stool consistency [75–81]. In accordance with the principles of the Declaration of Helsinki (64th WMA General Assembly, Fortaleza, Brazil, October 2013), we will underline to the participants that they can leave the study at any time for any reason if they wish to do so, without any consequences.

By filling in the questionnaires on symptoms of depression, anxiety and stress, participants may become more aware of these symptoms, therefore, become more anxious or depressed. In the occurrence of a psychiatric emergency, as observed during telephone or personal contact, the treating physicians (gynecologist, midwife, psychiatrist or general practitioner) will be informed as soon as possible (within < 12 h) about the health status of their patient, in order to take appropriate measurements. Furthermore, if a woman scores positively (e.g. “sometimes” or “yes, quite often”) on question 10 of the EPDS (“The thought of harming myself has occurred to me”), she will be advised by the CI to contact her general practitioner for support. Additionally, as stated previously, when a woman screens positive for “high risk” on suicidality (MINI), the woman’s general practitioner will be informed about the outcome of the MINI interview within a maximum of 12 h.

### Amendments

Any amendments of the protocol, including changes to study objectives, primary outcomes, study design, subject population, sample size or other study procedures that may impact the conduct of the study, need to be approved by the METC of the Radboud university medical center in Nijmegen. Non-substantial amendments, including minor corrections and/or clarifications that have no effect on the way the study is conducted, will not be notified to the accredited METC; these non-substantial amendments will be recorded and filed by the Sponsor.

### Confidentially

Data records containing personal participant information (e.g. informed consent forms) will be locked in file cabinets with limited access and kept separate from other study records identified by coded identification (ID), including the Baby's Cry Diary and other forms that link data to participants, to maintain participant confidentiality. Laboratory specimens will be coded with similar IDs (PIP01, PIP02, etc.) and kept in freezers with limited access. Electronic databases will be secured with password-protected access systems. Trial committee members will keep all results on questionnaires strictly confidential, and will only provide information to others on scores and the prevalence of anxiety and depression at the population level. Biological specimens transmitted via secure mail to collaborative universities for analysis are coded, and researchers at the collaborative universities will not have access to the subject ID code. All biological specimens will be destroyed after analysis.

### Access to data

Only members of the Trial Steering Committee and the supporting Research Assistant will have access to the final dataset. Investigators who are to conduct biological analysis will only have access to data by request and after approval by the Steering Committee. Data dispersed to collaborative investigators will be blinded to participants’ personal information.

### Serious adverse events

In accordance with the legal regulations of the METC and International Conference on Harmonization (ICH)-GCP regulations, the PI will report the serious adverse events (SAEs) to the accredited METC that approved the protocol, within 7 days of first knowledge of SAEs that are life threatening or result in death, followed by a period of a maximum of 8 days to complete the initial preliminary report. The PI will report all other SAEs to the METC within a period of a maximum of 15 days after the Sponsor has first knowledge of the SAEs.

### Premature termination of the study

The study will be terminated prematurely in the case of serious safety issues for participants. In the case that the study is ended prematurely, the PI will notify the accredited METC and the competent authority within 15 days, including the reasons for the premature termination.

### Ancillary and post-trial care

In accordance with the legal requirements in the Netherlands (Article 7 WMO and the Measure regarding Compulsory Insurance for Clinical Research in Humans of 23 June 2003), the Radboud University’s insurance will cover any potential injury that may be caused by the study.

### Dissemination policy

Members of the Steering Committee will analyze the data and write the final paper. The researchers will comply with the basic principles of the METC position on the disclosure/publication of research results obtained from studies involving human subjects: the results will be publicly disclosed without any restrictions; both positive and negative results will be published in a peer-reviewed journal. If the results are not eligible for a peer-reviewed publication, the research results will be publicly disclosed in the trial registry database. The researchers will undertake every attempt to reduce the minimum interval between completion of data collection and release of the results to participants and participating centers. We expect to share the first results (i.e. questionnaire data) with participants and participating centers within 3 months after completion of the study; we expect to share the results of analysis of biological specimens and to send the final paper to a journal within 1 year after study completion.

### Authorship

All research investigators of this pilot trial who provided substantial contributions to the design, conduct, analysis, interpretation and reporting of the study will be granted authorship on the final paper.

### Data sharing statement

The anonymized participant-level dataset and statistical codes to generate results will be made available upon reasonable request directly after acceptance of the final paper.

## Discussion and conclusion

Many expectant mothers experience symptoms of depression and anxiety during pregnancy, which can affect both the mother and the infant [1, 82, 83]. Most women remain untreated: only 14% of women with symptoms of prenatal depression or anxiety receive treatment [2].

There is a great need for accessible and effective (complementary) treatments that can be applied during pregnancy. There are indications that probiotics ingested during and after pregnancy can reduce symptoms of depression and anxiety postpartum [14]. Probiotics ingested by the mother may thus offer a promising and user-friendly intervention to complement current existing effective treatments aimed at reducing symptoms of anxiety or depression during pregnancy. The present study is the first study to investigate the feasibility and acceptability of a probiotic trial to reduce symptoms of maternal prenatal depression or anxiety in pregnant women. Results of this pilot trial will help make an informed decision whether or not to proceed with a full trial after the pilot trial, and if so, whether revisions should be made to the study protocol and procedures before conducting a full RCT.

### Potential underlying mechanisms

The influence of gut microbiota on maternal mood would be facilitated by the microbiota-gut-brain (MGB) axis. This bidirectional pathway integrates neural, immunological and hormonal signaling pathways between the gut and the brain [84, 85]. Microbial gut dysbiosis, an altered state of the gut microbiota composition, has been linked to anxiety and depression in pregnant and non-pregnant individuals [8, 9, 86, 87]. Probiotics, with their anti-inflammatory and neuroregulatory properties, may improve gut microbiota composition and functioning in pregnant mothers [10, 14, 88]. In turn, this may reduce symptoms of anxiety and depression [6, 14]. Furthermore, probiotics may also influence vaginal microbiota. Prenatal maternal stress has been linked to vaginal dysbiosis [89], and a state of vaginal dysbiosis can be positively influenced by maternal oral intake of probiotics [90].

### Maternal stress (i.e. reported and hair cortisol)

Next to potentially reducing symptoms of anxiety or depression, maternal prenatal probiotic intake may also decrease maternal stress (i.e. reported and hair cortisol). There are indications that stress is associated with an imbalance in intestinal microbiota, and that the ingestion of probiotics may restore such imbalance [91, 92]. For example, a study in healthy volunteers showed that probiotic ingestion resulted in lower levels of self-reported stress [86].

Additionally, the hypothalamic-pituitary-adrenal (HPA)-axis is highly activated in mothers with symptoms of stress, anxiety or depression, leading to elevated levels of cortisol, which accumulates in hair [93–96]. Since hair grows ~ 1 cm a month, higher concentration of hair cortisol is suggested to reflect the long-term activation of the maternal HPA-axis during pregnancy [96–101].

